**Methods:**

This is a two-arm randomized controlled trial recruiting 370 participants from a pool of high-risk patients receiving care at a home health agency. CareSage is a risk assessment system that utilizes both real-time data collected via a Personal Emergency Response Service and historical patient data collected from the electronic medical records. All patients will first be observed for 3 months (observation period) to allow the CareSage algorithm to calibrate based on patient data. During the next 6 months (intervention period), CareSage will use a predictive algorithm to classify patients in the intervention group as “high” or “low” risk for emergency transport every 30 days. All patients flagged as “high risk” by CareSage will receive nurse triage calls to assess their needs and personalized interventions including patient education, home visits, and tele-monitoring. The primary outcome is the number of 180-day emergency department visits. Secondary outcomes include the number of 90-day emergency department visits, total medical expenses, 180-day mortality rates, time to first readmission, total number of readmissions and avoidable readmissions, 30-, 90-, and 180-day readmission rates, as well as cost of intervention per patient. The two study groups will be compared using the Student *t* test (two-tailed) for normally distributed and Mann Whitney U test for skewed continuous variables, respectively. The chi-square test will be used for categorical variables. Time to event (readmission) and 180-day mortality between the two study groups will be compared by using the Kaplan-Meier survival plots and the log-rank test. Cox proportional hazard regression will be used to compute hazard ratio and compare outcomes between the two groups.

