### Participant Inclusion and Exclusion Criteria

Eligible participants are aged 65 years or older, English speaking patients who are receiving care or recently (within 3 months) discharged from PHH, and whose total health care costs fall within the middle 6th to 50th percentile (the middle segment of the cost acuity pyramid) of all patients seen at Partners Healthcare during the fiscal year 2016. The middle segment cutoffs for 2016 were projected based on 2011-2015 data from the analysis that was the precursor to this prospective study. Patients will not be excluded based on their disease condition as long as they fulfill the inclusion criteria stated above. Patients with artificial pacemakers and other implanted devices (as a precautionary measure against possible interference with the PERS device), currently on admission in a hospital or a long-term-care facility including Skilled Nursing Facilities, having severe dementia, Alzheimer’s disease or any other serious psychiatric illness (severe anxiety disorder or psychosis) will be excluded from this study.

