### Outcomes Measurement

The number of 180-day (6-month intervention period) emergency department visits in the intervention and control group will be measured as the primary outcome of interest for this study. Secondary outcomes will include the number of 90-day emergency department visits, the total cost of intervention provided to patients, total medical expenditure incurred during the study period (including total expenses attributable to the avoidable admissions), 180-day mortality rate, and time to first readmission. Furthermore, health care usage including emergency transport use, readmissions (30-, 90-, and 180-day), and the total number of avoidable admissions will be evaluated at the end of the study period. Following the methodology cited in Walsh et al and Segal et al, potentially avoidable admissions will be determined by analyzing the principal diagnosis ICD-9 code associated with each inpatient admission and categorizing the codes into 3 groups which are (1) those potentially avoidable in both institutional and non-institutional settings, (2) those potentially avoidable only in institutional settings, and (3) those which are not determined to be potentially avoidable [7,15].

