### Analysis

#### Sample Size

Based on a similar study with a comparable population by Coleman et al, which reported an odds ratio of 0.57 for 180-day hospital visits compared to matched controls, we are expecting to reduce the number of emergency department visits within a 180-day period by at least 35% in the intervention group compared to controls [17]. At 80% power and a type I error (alpha) of .05, we will need 185 participants in each of the study arms, accounting for a lost to follow-up of 15%.

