#### Statistical Analysis Plan

Data collected will be analyzed with data analysis (STATA, version 14) and statistical software (R, version 3.4.1). All the analyses will be conducted per the intention-to-treat principle. Descriptive statistics will be used to characterize the study sample, and we will summarize participants’ characteristics by study arm. The two study groups (intervention and control) will be compared by the Student *t*-test (two-tailed) for normally distributed and the Mann Whitney *U* test for skewed continuous variables, respectively. The chi-square test will be used for categorical variables. Time to event (readmission) and 180-day mortality between the two study groups will be compared by using the Kaplan-Meier survival plots and the log-rank test. Cox proportional hazard regression will be used to compute hazard ratio and compare outcomes between the two groups. We will also conduct subgroup analyses based on enrollment in iCMP during the 6-month intervention period. Fixed and per-patient intervention costs will be calculated from PHH records. The monthly per-patient costs of health care services and out-of-pocket costs will be combined, and multivariate analyses comparing this sum (potential cost offset) for intervention versus usual care patients will be conducted.

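### Kaplan-Meier curves for first readmission, with no stated handling of death before readmission, would overstate absolute readmission risk if deaths are censored; the log-rank and Cox comparisons remain valid

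*Protocol article*

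**What the plan says.** The Statistical Analysis Plan section of the article fixes the method for readmission and for death in one sentence: "Time to event (readmission) and 180-day mortality between the two study groups will be compared by using the Kaplan-Meier survival plots" and the log-rank test. The next sentence adds that "Cox proportional hazard regression will be used to compute hazard ratio and compare outcomes between the two groups".

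The Outcomes Measurement section names "180-day mortality rate, and time to first readmission" as separate secondary outcomes. The abstract also lists "30-, 90-, and 180-day readmission rates" among the secondary outcomes, and the Statistical Analysis Plan assigns categorical variables to the chi-square test.

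The article does not say what happens to a patient who dies before any readmission. It names no competing-event method and no composite of readmission or death, and it gives no expected readmission or mortality rate.

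**The concern.** A patient who dies without having been readmitted can no longer be readmitted. In a Kaplan-Meier analysis of readmission alone, that patient normally leaves the risk set as censored. The estimator then treats the patient as someone who would later have been readmitted at the same rate as those still alive. One minus the Kaplan-Meier curve therefore estimates the risk of readmission in a setting where nobody dies first, which exceeds the proportion actually readmitted.

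The fixed-time readmission rates treat the same patient differently. A patient who dies first is simply not readmitted by day 30, 90 or 180 and counts as a good result. If mortality differs between arms, the arm with more deaths shows a lower rate even when the hazard of readmission is the same in both.

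At stake is the reading of secondary outcomes in a cohort for which "Eligible participants are aged 65 years or older" and which is under home health care or recently discharged from it. The trial itself treats 180-day mortality as worth comparing. A curve that is somewhat too high, next to rates that improve when patients die, is hard to read as benefit or harm.

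**Working it through.** **Inputs.** There is no figure in the plan to reproduce: the article states no readmission rate, mortality rate or hazard ratio for these outcomes. The sample-size figure of 185 per arm concerns emergency department visits and is not involved. The 180-day window is taken from the primary outcome, "The number of 180-day (6-month intervention period) emergency department visits". All event rates below are assumptions.

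**Model.** Independent constant hazards over the 180-day window, with cumulative values a (readmission) and b (death without prior readmission):

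- Risk read from Kaplan-Meier with deaths censored: KM = 1 − exp(−a)
- Actual proportion readmitted: CIF = a/(a+b) × [1 − exp(−(a+b))]
- Net 180-day death risk: 1 − exp(−b)

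**Step 1. Fix the Kaplan-Meier risk at 30% and vary mortality.** Here a = −ln(0.70) = 0.3567.

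| Net death risk | b | CIF | KM excess |
|---|---|---|---|
| 2% | 0.0202 | 29.7% | 0.3 points |
| 5% | 0.0513 | 29.3% | 0.7 points |
| 10% | 0.1054 | 28.6% | 1.4 points |
| 20% | 0.2231 | 27.1% | 2.9 points |

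For the 5% row: 0.3567/0.4080 × [1 − exp(−0.4080)] = 0.293.

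**Step 2. Fix the actual proportion readmitted at 40% and vary the proportion dying first.** Here a+b = −ln(1 − 0.40 − D), and a is the share 0.40/(0.40+D) of that sum.

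| Dying first (D) | a | b | KM | KM excess | Net death risk implied |
|---|---|---|---|---|---|
| 5% | 0.531 | 0.066 | 41.2% | 1.2 points | 6.4% |
| 10% | 0.555 | 0.139 | 42.6% | 2.6 points | 12.9% |
| 15% | 0.581 | 0.218 | 44.1% | 4.1 points | 19.6% |

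The last column matters: dying first is a smaller quantity than net mortality, so the lower rows assume heavy mortality.

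**Step 3. Same readmission hazard, different death hazard.** Keep a = 0.555 and start from the 10% row.

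| Death hazard | KM | Crude readmission rate (CIF) | Dying first | Readmission or death = 1 − exp(−(a+b)) |
|---|---|---|---|---|
| halved | 42.6% | 41.3% | 5.2% | 46.4% |
| as is | 42.6% | 40.0% | 10.0% | 50.0% |
| doubled | 42.6% | 37.6% | 18.8% | 56.5% |

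Doubling the death hazard lowers the crude readmission rate by 2.4 points, while the composite rises by 6.5 points. The Kaplan-Meier value does not move, so a log-rank or Cox comparison correctly reports no difference in the readmission hazard.

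**Step 4. Effect on the between-arm difference.** Assume a control Kaplan-Meier risk of 30%, net death risk 5% and a readmission hazard ratio of 0.65. The Kaplan-Meier difference is 30.0% − 20.7% = 9.3 points.

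| Death hazard ratio | CIF difference | CIF risk ratio |
|---|---|---|
| 0.65 | 8.9 points | 0.70 |
| 1 | 9.1 points | 0.69 |
| 1.5 | 9.3 points | 0.68 |

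The Kaplan-Meier risk ratio is 0.69. Under these assumptions the between-arm contrast barely changes; what changes is the height of each curve.

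**The case against.** **The censoring rule is not in the text.** A reader might infer that the plan has decided to censor deaths. It has not said so, and a fuller plan that is not shown may set a rule. This stands: censoring at death is the usual consequence of the named estimator, not a statement in the article. The choice of Kaplan-Meier for readmission is stated, however, and that is what the point addresses.

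**The planned tests are sound.** A reader might also infer that the log-rank and Cox results are biased. They are not biased merely because deaths are censored. With deaths censored they compare the cause-specific hazard of readmission, which is a legitimate question; Step 3 shows this. The limit is only that such a hazard ratio does not translate directly into a ratio of risks.

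**Mortality is already reported, and the crude rate is already a cumulative incidence.** Both are largely true. With complete follow-up, the crude 180-day rate is the cumulative incidence at that time. The Sample Size section allows for 15% loss to follow-up, though, so completeness cannot be taken for granted. Separate mortality figures also do not give readmission-or-death, because some deaths follow a readmission.

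**The cohort and mechanism.** It is tempting to call this a frail elderly cohort with high mortality. In the Introduction that term describes a segment in a cited study. This trial enrols patients "whose total health care costs fall within the middle 6th to 50th percentile" and excludes current inpatients, long-term-care residents and people with severe dementia. The intervention's stated goals are education, adherence and symptoms treatable in outpatient care. The documents therefore do not support an expected mortality difference between arms.

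**The size is small at low mortality.** This stands. Under Step 4, with 185 per arm, the standard error of the risk difference is about √(0.293×0.707/185 + 0.202×0.798/185) = 4.5 points, far larger than the shifts of up to 0.4 points.

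**Conclusion.** The point holds for the absolute risk shown in the readmission curve and for the interpretation of the crude rates. It does not reach the validity of the log-rank or Cox comparison, the primary outcome or the sample size.

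If deaths are censored, the curve overstates readmission risk whenever anyone dies first. The excess is below 1 point at 5% mortality or less with a 30% readmission risk. It reaches 1.2 to 4.1 points only at a 40% readmission risk with 5 to 15% dying first. The crude rates can move by about 2 points in favour of the arm with more deaths, but only if its death hazard is about double. These figures rest on assumed rates, constant independent hazards and a 180-day window. The matter is worth correcting because the better method is standard and nearly free, not because a large error has been shown.

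**What to change.** - State how a death before first readmission is handled.
- Replace the Kaplan-Meier readmission curve with cumulative incidence curves by arm (Aalen-Johansen), with death as a competing event. Kaplan-Meier remains right for mortality.
- Keep the log-rank test and Cox model for readmission, and label both as comparisons of the cause-specific hazard.
- Beside each 30-, 90- and 180-day readmission rate, report the proportion readmitted or dead by that day.
- A Gray test is optional.

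The cost is a few lines of plan wording and code in the two packages already named, plus one extra composite to report. Mortality and readmissions are already to be extracted from the health system's databases, so no new data are needed.

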Health care utilization is unevenly distributed among Medicare beneficiaries. A study analyzing trends in Medicare spending concentration over a 30-year period showed that as Medicare spending increased from US $14.5 billion to US $295.2 billion from 1975 to 2004, the top 5% and 1% of beneficiaries accounted for 43% and 15.5% respectively of all Medicare expenditure in 2004 (US $125 billion and US $45.3 billion, respectively) [9]. Using the 2011-2012 Medicare claims data, another study by Joynt et al segmented beneficiaries into 6 potentially actionable groups [10]. This study found that the frail elderly (age ≥65 years and the presence of at least two conditions indicative of frailty) were most likely to be in the highest cost segment with their costs driven by inpatient and post-acute care services. More recently, another study divided older patients based on their health care costs (from most to least expensive) into 3 segments and organized them into a cost pyramid comprising of the following categories: top 5%, middle (6%-50%) and bottom segments (51%-100%) [11,12]. The authors examined cost data from 2010 through 2015, studying a cohort of patients going through the health care system and evaluated their health care utilization from one year to the next [12]. The study demonstrated that the middle segment represented the most expensive segment over time [12].

Currently, many health care organizations employ intensive population health management strategies which are targeted at patients in the top segment of the cost acuity pyramid to control costs. One such example is the integrated care management programs (iCMP) at Partners Healthcare that provides specialized care to high risk patients with multiple comorbid conditions [13]. Due to the finding that these high-cost patients transition to lower cost segments in subsequent years, a modified strategy is to target population health interventions at patients in the middle segment. Therefore, in this study, we evaluate the impact of CareSage, a risk assessment system, combined with personalized and timely interventions on the health care utilization and associated costs in older patients in the middle segment of the health care cost pyramid.

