## Methods

### Study Design

The study will be implemented as a two-arm randomized controlled trial with two study periods, namely an initial 3-month observation period followed by a 6-month intervention period. Each participant will be in the study for a total of 9 months. At the beginning of the observation period (baseline), enrolled patients will be randomized into two groups, either the intervention or control group. During the observation period, the CareSage algorithm will calibrate using patient data (from both groups) collected from a Personal Emergency Response Service (PERS) device. During the 3-month observational period, all participants will complete the baseline study assessments and will continue to receive usual care from their care providers, but no study interventions will be administered. The 6-month intervention period begins immediately after the observational period. During the intervention period, patients in the intervention group will be actively monitored by CareSage and will receive personalized interventions when flagged as “high” risk for emergency transport. Patients in the control group will receive care as usual during the intervention period. Assessments of study outcomes will be made at the end of the 9-month study period. Figure 1 shows the research design.

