### Participants

A total of 370 participants will be recruited from a pool of patients receiving care at Partners Health at Home (PHH)—a home health service that offers general care as well as specialized services to help patients manage chronic conditions. PHH consists of a network of qualified clinicians who deliver care designed to meet the unique needs of each patient, with the goal of optimizing independence and quality of life. On average, most patients are on PHH service for 2-3 months, but the duration may vary based on the patients’ condition and needs. Patients who are considered likely to benefit from PHH services are typically referred to the program by their care providers. PHH services patients who are receiving care from any of the Partners Healthcare Network of hospitals (comprising of 7 major hospitals, including 2 large academic centers and several community health centers) are eligible for this study. In addition, a subgroup of patients from PHH who may be enrolled in other care management programs such as iCMP will be included in the study.

During the study, staff will periodically review previous PHH admissions and identify potential study participants. Identified patients will be prescreened over the phone to gauge interest and confirm eligibility. Eligible and interested patients will be enrolled by study staff at the patient’s home. Screening, informed consent, randomization and survey completion will occur at this enrollment visit. During this visit, patients will be given a PERS device to use for 9 months. Patients will be instructed to wear the device continuously throughout the study period.

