
Participants in the control group will receive the following:

Passive Monitoring: These participants will continue to use the PERS system. After the 3-month observation period, the CareSage algorithm will continue to only passively monitor control group participants but will not alert the study nurse about their risk for emergency transport. The data from CareSage will continue to be captured at the backend and will be collected at the end of the study.Care as usual: Participants will continue to receive medical treatment and discuss any questions or concerns with their care providers as usual. There will be no triage for control group participants.

Participants in the intervention group will receive the following:

Active monitoring: Patients in the intervention group will be assessed by the Web-based CareSage risk assessment system, which can identify when a patient is at risk for emergency transport in any upcoming 30-day period. Patients identified as “high risk” will receive nurse triage calls and, depending on their needs, tailored interventions per a stepped-care approach (Figure 2). The principal goals of the intervention will be to address knowledge gaps in disease self-management, ensure compliance with medications and healthy diet, and identify recurrent symptoms amenable to treatment on an outpatient basis to prevent readmissions.Nurse Triage Call*:* During the intervention period, “high-risk” patients will be called by a trained study nurse to assess the physical and psychological patient’s needs using a health needs assessment guide (Multimedia Appendix 2) developed by the study team. These 15-30-minute telephone calls will focus on how the patient is feeling, adherence to treatment plans, and connect the patient to any available resources (primary care physician, dietician etc) as needed.

Tailored PHH Interventions The PHH interventions consist of multiple components tailored to individual patients based on the needs identified during nurse triage call. The complete intervention decision pathway is depicted in Figure 3. There are 3 interventions that the study nurse may offer.

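### The only named subgroup is defined by iCMP enrolment during the intervention period, after randomisation, so its estimates are open to selection bias

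*Protocol article*

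**What the plan says.** The subgroup sentence is in the protocol article, Statistical Analysis Plan: "We will also conduct subgroup analyses based on enrollment in iCMP during the 6-month intervention period". No other subgroup is named.

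The timing comes from two other sections:

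- Study Design: "At the beginning of the observation period (baseline), enrolled patients will be randomized into two groups, either the intervention or control group". The observation period lasts 3 months, and then "The 6-month intervention period begins immediately after the observational period".
- Outcomes Measurement: "The number of 180-day (6-month intervention period) emergency department visits in the intervention and control group will be measured as the primary outcome".

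Four places bear on who is in iCMP and why:

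- The Introduction describes "integrated care management programs (iCMP) at Partners Healthcare that provides specialized care to high risk patients", and gives it as an example of strategies "targeted at patients in the top segment of the cost acuity pyramid to control costs".
- Participants says that "a subgroup of patients from PHH who may be enrolled in other care management programs such as iCMP will be included in the study", without saying when membership is assessed.
- Intervention says that the study nurse's calls to flagged patients will, among other things, "connect the patient to any available resources (primary care physician, dietician etc) as needed". The same section says that controls get no triage.
- Study Rationale, in the Discussion, says that the study aims to keep middle-segment patients from moving into the higher cost segment.

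The Randomization section describes permuted blocks and mentions no stratification by iCMP.

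**The concern.** A subgroup keeps the protection of randomisation only if membership is fixed before treatment can influence it. Here membership is read from the same six months in which the intervention is given and the emergency department visits are counted.

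The article's own text suggests three ways in which membership could depend on arm or on outcome:

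- Nurse triage, which only the intervention arm receives, links patients to resources and could raise enrolment in that arm.
- An intervention that succeeds in keeping patients out of the high-cost segment could lower enrolment in that arm.
- Emergency visits during the period could themselves lead to enrolment.

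In each case, patients within a stratum are no longer comparable between arms. An apparent benefit, harm or difference between strata could then come from who was sorted into which stratum. This would affect any statement about whether CareSage works differently in patients who are in iCMP.

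**Working it through.** **Step 1: time line.** Randomisation is at month 0. The observation period covers months 0 to 3, and the intervention period months 3 to 9. The primary outcome window is the same 180 days as the intervention period, and so is the window that defines the subgroup. As written, the defining window opens three months after randomisation and coincides with both treatment and outcome.

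**Step 2: inputs for size.** The article gives no iCMP rate, entry rule or referral path, and no figure for the subgroup, so there is no stated figure to reproduce. Every input below is an assumption.

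The simulation used 2,000,000 patients randomised 1:1:

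- Frailty *u* follows a gamma distribution with shape 1 and mean 1.
- Visits are Poisson with mean 0.6 × *u* × RR^arm. The true rate ratio RR is the same for everyone.
- logit P(iCMP) = logit(0.2) + ln(OR_arm) × arm + ln(2) × (*u* − 1). This gives 21.7% enrolment among controls.
- Where visits drive enrolment, 0.5 × (visits − 0.5) is added and OR_arm = 1. This was run once without and once with the frailty term.

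The estimate in each stratum is mean visits in the intervention arm divided by mean visits in the control arm. The contrast is the iCMP ratio divided by the non-iCMP ratio. Its true value is 1.00 throughout.

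**Step 3: results.**

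| Enrolment mechanism | True RR 1.00: iCMP / non-iCMP (contrast) | True RR 0.65: iCMP / non-iCMP (contrast) |
|---|---|---|
| Arm has no effect (as with status at randomisation) | 1.00 / 1.00 (1.00) | 0.65 / 0.65 (1.00) |
| Intervention halves the odds | 1.121 / 1.060 (1.06) | 0.723 / 0.689 (1.05) |
| Odds × 1.5 | 0.932 / 0.964 (0.97) | 0.615 / 0.628 (0.98) |
| Odds × 2 | 0.893 / 0.930 (0.96) | 0.577 / 0.606 (0.95) |
| Odds × 3 | 0.837 / 0.895 (0.94) | 0.547 / 0.577 (0.95) |
| Visits raise enrolment, no frailty term | 1.00 / 1.00 (1.00) | 0.630 / 0.682 (0.92) |
| Visits raise enrolment, with frailty term | 1.00 / 1.00 (1.00) | 0.660 / 0.678 (0.97) |

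Both strata can move in the same direction. If the intervention raises enrolment, the patients it adds are on average less frail than those already in iCMP, but frailer than those left outside. Mean visits in the intervention arm then fall in both strata, although nobody's visit rate has changed.

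The visit-driven mechanism creates no false effect under a true null. It distorts the estimates only when there is a real effect.

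**Step 4: a hand check at an extreme.** Suppose 20% of patients are high risk (2.0 visits) and 80% low risk (0.75 visits), with no treatment effect. All high-risk intervention patients, half of the high-risk controls and no low-risk patients are in iCMP.

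- Control, non-iCMP: (0.10 × 2.0 + 0.80 × 0.75) / 0.90 = 0.80 / 0.90 = 0.889.
- Intervention, non-iCMP: 0.750. Ratio 0.750 / 0.889 = 0.844, an apparent reduction of about 16%.
- iCMP stratum: 2.0 against 2.0, ratio 1.00, which is unbiased.
- Contrast: 1.00 / 0.844 = 1.19.

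This is a worst case. It shows that a false contrast can arise even when one of the two strata is estimated correctly.

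**The case against.** The strongest reply is that the sentence may mean something harmless. The six-month phrase could describe the period over which outcomes are analysed, with iCMP status taken at entry. The Participants section does speak of iCMP membership as a feature of patients who are included. This reading is possible. However, the sentence attaches the period to enrolment, and Participants gives no time point. If entry status was meant, the same one-sentence correction is still needed.

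The second reply is that the mechanism is inferred. That stands. No section says that study nurses refer patients to iCMP. The resources named are a primary care physician and a dietician, and the primary care provider is contacted to approve an in-person assessment or telemonitoring. Controls keep their usual providers and could also enter iCMP.

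A reader might therefore infer that the subgroup estimates are biased as a matter of fact, or biased by the 16% of the hand check. The documents support neither inference. Bias requires arm or on-treatment outcome to change enrolment. For the arm route, enrolment must also be related to risk. The text makes this plausible but does not show it. Nor must both strata be wrong, as the hand check shows.

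Third, this is an additional analysis. iCMP appears in none of the stated aims or outcomes, and no sample size depends on it. That also stands, and it limits the severity.

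**Conclusion.** The point holds as a risk built into the stated definition. As written, the plan conditions on a variable observed after randomisation, over the same window as treatment and primary outcome. The article's description of iCMP, of the trial's aim and of one-sided nurse triage makes it plausible that arm or outcome affects membership.

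The size cannot be derived from the documents. Under the simulation's assumptions, a true null appears as anything from 1.12 / 1.06 to 0.84 / 0.90 (iCMP / non-iCMP). The contrast is off by at most about 8% (0.92 against a true 1.00). Without any influence of arm or outcome on enrolment, the bias is zero.

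A reader might also infer that the trial's main result is compromised. It is not: the primary comparison is by randomised arm under intention to treat and does not use iCMP status. Severity is moderate.

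**What to change.** Replace the subgroup sentence in the Statistical Analysis Plan section with one that does three things:

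1. Defines the subgroup by iCMP status at or before randomisation.
2. Specifies a test of the arm-by-baseline-iCMP interaction, reported with the two stratum estimates.
3. Reports iCMP enrolment during the intervention period descriptively by arm, as a concurrent programme and not as a grouping variable.

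With membership fixed at randomisation, the simulation returns the true rate ratio in both strata (1.00 / 1.00 and 0.65 / 0.65).

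The cost is small. Recruitment, treatment and follow-up do not change. Enrolment was under way when the article was written and analysis is planned for the end of the study, so the change could be made before analysis. There are two drawbacks. The iCMP stratum may contain fewer patients, because those who join later no longer count towards it. Baseline iCMP status must also be retrieved: the Data Collection section does not list it among the outputs of the screening query, so its availability is an assumption to confirm.
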